### Study objectives and outcomes

The primary objective of the ALCAT trial is to demonstrate that acetyl-DL-leucine is effective at improving motor function measured by the SARA total score. The primary efficacy endpoint is the absolute change in the SARA total score from period-level baseline to the end of the 6-week treatment period, i.e. the difference between post-treatment values at the end of each treatment period and the corresponding period-level baseline values:$$ \mathrm{Delta}\ \left(\mathrm{SARAtotal}\right) = \mathrm{SARAtotal}\ \left(\mathrm{post}\hbox{-} \mathrm{treatment}\right)\ \hbox{--}\ \mathrm{SARAtotal}\ \left(\mathrm{period}\ \mathrm{baseline}\right) $$

We presume a minimum clinically relevant difference in the SARA total score of 1.5 points. The secondary objectives are to determine whether Acetyl-DL-Leucine is effective at:improving motor function measured by the Spinocerebellar Ataxia Functional Index (SCAFI) and SARA subscore itemsimproving QoL, as well as the common comorbidities depression and fatigue.

The secondary efficacy outcome measures will be absolute changes in the subscores of SARA as well as the SCAFI total score and subscores of SCAFI (8 MW testing gait, 9HPT testing limb ataxia and the PATA rate task for speech). Furthermore, patient-reported outcomes using the EuroQoL 5 dimensions and 5 level version (EQ-5D-5 L), Beck’s Depression Inventory (BDI-II) as well as the Fatigue Severity Scale (FSS) will be recorded.

For all these scores, the treatment effect will be assessed at the end of each treatment period and at the post-treatment follow-up visit.

During the whole study period any AE (any untoward medical occurrence, including an abnormal laboratory finding, regardless of its causal relation to the study treatment) will be recorded.

#### Ataxia rating scales

The clinical severity of ataxia will be assessed by two different clinical ataxia rating scales — namely SARA [24] and SCAFI [25, 26]. The scores will be assessed by the investigators. Both scales assess ataxia and dysarthria, and are widely used in clinical practice [26] and clinical trials covering the whole range of impaired motor function in ataxic patients. The scales are measured at each clinic visit.

The SARA total score serves as a key inclusion criterion measuring the severity of ataxia prior to enrollment. The SARA total score has eight categories reflecting neurologic manifestations of CA. Each category represents a crucialmovement feature in CA rated by an examiner (gait, stance, sitting, speech disturbance, finger chase, nose-finger test, fast alternating hand movements, heel-shin slide) resulting in a score ranging from 0 (no ataxia) to 40 points (most severe ataxia). It is a reliable and valid clinical scale with a high internal consistency that measures the severity of ataxia and increases with disease stage [25, 27, 28].

The SCAFI includes the 8 MW testing gait, the 9HPT testing limb ataxia and the PATA rate task for speech and therefore represents vital movement features. In contrast to the SARA, the SCAFI uses a timed approach rated by an examiner. After the assessment, raw scores are transformed into reciprocals and converted into subtest Z-scores. The resulting SCAFI is defined as the arithmetic mean of all three Z-scores.

#### Patient questionnaires for quality of life, depression and fatigue

A self-administered questionnaire to evaluate QoL, namely the EQ-5D-5 L [29] (multiple choice questionnaire and a visual analogue scale) will be used. The EQ-5D-5 L is a standardized measure of health status that provides a simple, generic measure of health for clinical and economic appraisal and consists of 2 parts — the EQ-5D descriptive system and the EQ visual analogue scale (EQ-VAS). The EQ-5D-5 L descriptive system comprises the following 5 dimensions: mobility, self-care, usual activities, pain/discomfort and anxiety/depression. Each dimension has 5 levels: no problems, slight problems, moderate problems, severe problems, and extreme problems.

As depression and fatigue are known common comorbidities in patients with CA, trial participants are instructed to complete the BDI-II [30–32] and FSS [32] questionnaires at each clinic visit. The BDI-II is a multiple choice self-report inventory for measuring the severity of depression and is composed of items related to symptoms of depression such as hopelessness and irritability, emotions such as guilt or feelings of being punished, as well as physical symptoms such as fatigue, weight loss and lack of interest in sex. The FSS captures the patient’s experience of mental or psychological fatigue and how it interferes with performing certain activities (exercise, work and family life). It is a self-reporting scale of 9 items. The mean of all answered items represents the fatigue severity.

#### Laboratory examinations

A routine blood sample will be taken to exclude liver or kidney failure, and a pregnancy test for women of childbearing potential will be performed. A pregnancy test is not required for postmenopausal (amenorrhea >12 months), surgically sterilized or hysterectomized women. The following laboratory parameters will be assessed (but not routinely documented in the CRF): sodium, potassium, creatinine, serum bilirubin level, AST, ALT, urea, ALP, TSH, hemoglobin, erythrocytes, hematocrit, thrombocytes, leukocytes, pregnancy test for women of childbearing potential. In a case of an AE, laboratory parameters will be documented. The total amount of blood taken per subject during the entire trial will be approximately 20 ml. Laboratory examinations are carried out at visit 1, visit 4, visit 5 and visit 7.

### Concomitant drug and non-drug therapies

Trial participants should not begin physiotherapy or speech therapy while they are enrolled in the trial. If they are already under therapy, the amount of sessions of physiotherapy and speech therapy (measured in hours of therapy per week) will be documented in the patient’s medical record and in the case report form (CRF) during the trial and for 6 months prior to randomization. To adhere to the protocol, the non-pharmacological concomitant therapy should be continued with the same intensity while the patient is enrolled in the trial.

Guided by the eligibility criteria, the administration of 4-aminopyridine, Riluzole, Varenicline, Gabapentin or Chlorzoxazone is not allowed during the trial because of a possible beneficial effect in CA.

### Participation discontinuation and follow-up of participants ‘off protocol’

If a participant withdraws from the study, the reason will be documented. ‘Off protocol’ is defined as those study participants who cease trial medications on clinical grounds. Regardless of the decision to continue with study medication, these participants will be asked to participate in all scheduled follow-up appointments, as if they were maintaining full participation, in order to prevent further missing data. Those who are unwilling or unable to do this will be asked to agree to a phone or mail follow-up, and/or permission for study staff to continue ascertainment of outcomes.

### Statistical planning and analyses

#### Power considerations and sample size calculation

The sample size was calculated on the basis of the primary hypothesis, using our own preliminary case series data (13 patients [17]) and a similar placebo-controlled trial (20 patients [7]) investigating the efficacy of varenicline on the change in SARA total score in patients with SCA 3. Hence, assuming a minimum clinically relevant difference in the SARA total score of 1.5 points [25] to be detected (i.e. the absolute change on acetyl-DL-leucine is 1.5 score points better than the change on placebo) and a standard deviation of the individual SARA change of 4.2, a sample size of 86 (85 is calculated but 2 sequences are needed) in total is will have 90% power to detect a difference in means of 1.5, using a paired *t*-test with a 0.05 two-sided significance level [Software used: nQuery Advisor 7.0]. On the basis of our experience with patient compliance in previous studies, we expect a dropout rate of about 20%. Thus, a total of 108 patients have to be enrolled. With a proportion of about 50–55% recruited patients out of the number to be screened, about 200 patients have to be assessed for eligibility. There is no interim analysis planned for this study.

#### Statistical analyses for primary and secondary endpoints

Efficacy analyses are based on the intention to treat (ITT) principle in that all participants randomized will be analyzed according to the treatment sequences to which they were allocated and irrespective of the extent of intervention received. In this study, the term ‘full analysis set’ is used to describe the analysis set, which is as complete as possible and as close as possible to the ITT ideal of including all randomised participants (i.e, the ITT population). All statistical tests are two-sided, and the significance level alpha is set to 5%.

For the primary efficacy outcome change in SARA total score (DeltaSARA), the null hypothesis will be tested that there is no difference in mean change between placebo and acetyl-DL-leucine.

Absolute change, calculated as the difference between the period-level baseline score and the score measured at the 2-week and 6-week visits of the acetyl-DL-leucine/placebo period, will be considered for a model-based primary efficacy analysis. If not revised in the statistical analysis plan (SAP), a linear mixed effects model for DeltaSARA will be performed (fixed effects: factor for treatment, visit, treatment-by-visit interaction, and mean of both period-level baseline SARA total scores as covariate; normally distributed patient-specific random intercepts and slopes) in order to deal with repeated measurements within periods and measurements not made at equivalent times in each subject due to unscheduled or missed clinic visits. This subject-specific modelling approach allows individual change scores over time to be calculated. To analyse the differences between both interventions at the end of the 6-week treatment period, 95% confidence intervals will be provided to quantitatively describe treatment effects.

Sensitivity analyses will be performed on a per protocol approach which takes into account treatment adherence and compliance with the trial protocol. Additional efficacy analyses adjusting for genetic vs. sporadic CA, gender, age, or trial site, will be performed. In addition, the robustness of the overall efficacy result will be investigated by analyses adjusting for the amount of physiotherapy the patient received when he or she was enrolled in the trial (which should be comparable to the amount received before randomization), as considered appropriate during the blinded data review and depending on the data quality. Since this analysis will also be based on variables measured after randomization, the susceptibility for bias will be given consideration and will be discussed.

In case of a statistically significant primary efficacy result, confirmatory testing will be extended to the EQ-5D-5 L (VAS and descriptive scale). SCAFI (total score and 3 subscores), SARA subscale items, as well as patient-reported outcomes BDI-II and FSS are not considered in the hierarchical multiple testing procedures. Descriptive comparisons between treatment groups at the end of the 6-week acetyl-DL-leucine/placebo period will be performed using a two-sided Wilcoxon signed rank test, and additionally, Hodges-Lehmann estimation of the location shift between the two groups will be provided, as considered appropriate based on the blinded data. The same non-parametrical tests will be employed to estimate treatment differences at the follow-up visit 8 (close-out visit). Further methodological details will be provided in the SAP.

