## Background

Cerebellar ataxia (CA) is a frequent and often disabling syndrome which can severely impair motor functioning and quality of life (QoL) [1]. CAs are most often caused by neurodegenerative disorders of the cerebellum which are either hereditary or non-hereditary (sporadic); all in all, about 50% of the cases are sporadic. Studies suggest that the overall prevalence of CA in Europe is similar to that in Japan and may approach 20:100,000, i.e., 15,000 patients in Germany (www.ataxie.de) [2]. Due to the various etiologies and different courses of the diseases, there are no robust epidemiological data on CA-related mortality.

The leading clinical symptoms of CA are disturbances of stance or gait (>85%) with recurrent falls, limb ataxia with severe functional impairment of arm and hand movements, dysarthrophonia with impaired oral communication abilities, and ocular motor disturbances with impaired vision [1]. Further, most types of CA are progressive and therefore become more disabling in the course of the disease, severely impairing QoL and functioning [1]. In addition to functional impairment, CA also affects cognitive and psychosocial abilities and limits the ability to perform tasks of daily life. It is thus a severely disabling condition, progressively restricting autonomy and social participation. The care that is required is frequently provided by the family, thus further increasing the socioeconomic burden of disease [3]. Major cost components relevant for patients with CA are informal care, early retirement because of permanent disability, drugs, orthopedic devices, and rehabilitation. As the disease progresses, quality of life decreases and utilization of health resources increases [4].

No medication has yet been proven effective for the symptomatic or even causative treatment of degenerative CA [5]. Beneficial effects of Varenicline and Riluzole have been reported [6–8]. However, according to a consensus paper on management of degenerative CA, these findings need to be further confirmed in further placebo-controlled trials, in particular long-term and disease-specific studies [8, 9]. To date, the only treatment recommendation for CA is physiotherapy [10] and new therapeutic options are needed.

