
## Methods/Design

### Trial design and setting

The ALCAT trial is an investigator-initiated, multicenter, randomized, double-blind, placebo-controlled, 2-treatment 2-period crossover phase III trial. The study was initiated at the Department of Neurology and the German Center for Vertigo and Balance Disorders (University of Munich) and the Friedrich-Baur-Institute, and has been subsequently extended to other study sites located in Germany (University of Tuebingen, University of Essen, and DZNE Bonn), Austria (Innsbruck) and will be expanded to the Netherlands (Nijmegen). The study has been approved by the responsible ethics committees in Germany (project number 248–15 fed) as well as the ethics committee in Austria (project number AN2015–0252 355/2.1) and has been submitted to the ethics committee in the Netherlands. Furthermore, the study has been approved by the legal medical regulatory authorities (Federal Institute for Drugs and Medical Devices, in German: Bundesinstitut für Arzneimittelsicherheit und Medizinprodukte - BfArM in Germany, Austrian Agency for Health and Food Safety Ltd. AGES, in German: Österreichische Agentur für Gesundheit und Ernährungssicherheit GmbH in Austria, Central Committee on Research Involving Human Subjects, in Dutch: Centrale Commissie Mensgebonden Onderzoek – CCMO in the Netherlands). The first patient was randomized on January 25, 2016. The ALCAT trial is conducted in accordance with the International Conference for Harmonisation (of Technical Requirements for Pharmaceuticals for Human Use) - Good Clinical Practice Guideline (ICH-GCP) and the Declaration of Helsinki. The trial has been prospectively registered at www.clinicaltrialsregister.eu (EudraCT no. 2015–000460–34) and https://www.germanctr.de (DRKS-ID: DRKS00009733) on January 15, 2016. Patient insurance for the study has been arranged (policy number for Germany 39 130537 03026, for Austria 07208763–1, for Netherlands 081 50474–14005).

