### Randomization, concealment, and blinding

Participants fulfilling the entry criteria at screening will be randomly assigned in a ratio of 1:1 to receive one of the two treatment sequences (active treatment followed by placebo, or vice versa). The randomization technique is based on permutated balanced blocks with random block length. The procedure considers stratification by study site and by genetic vs. sporadic CA to ensure balanced strata, maintaining allocation concealment. The allocation sequence will be generated by an independent person from the Institute of Medical Informatics, Biometry and Epidemiology (IBE) of the University of Munich who is not involved in assessing study outcomes. Neither the investigators nor other trial staff (data analysts, statisticians) or the patients will be informed about the treatment sequences to which a patient is allocated, and neither has access to the randomization list. Thus, randomisation will be conducted without any influence of the investigators or trial staff. The IBE will provide an internet-based, password-protected randomization tool (“Randoulette”: https://wwwapp.ibe.med.uni-muenchen.de/randoulette), which chooses the treatment sequence for a new patient who fulfills the eligibility criteria and has signed the informed consent. Randoulette will register the patient by his or her screening number, gender, year of birth and strata before the allocated package number is provided. The current trial is subject— and investigator-blinded. Patients, clinicians, core laboratories, and trial staff (including data analysts and statisticians) will be unaware of the treatment that the participant will take during both double blind treatment periods.

Un-blinding will occur in the event of a clinical emergency in which the knowledge of the medication being taken is essential for the participant’s clinical management. The investigator is supplied with an opaque sealed envelope for each participant that contains the corresponding treatment sequence for unblinding. Alternatively, the randomization code can be broken using Randoulette.

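### The default primary model for this two-period crossover has no period effect, which costs some precision if sequences stay balanced and biases the estimate if completers differ by sequence

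*Protocol article*

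**What the plan says.** The section on trial design and setting describes a "randomized, double-blind, placebo-controlled, 2-treatment 2-period crossover phase III trial". Under randomization, patients are "randomly assigned in a ratio of 1:1 to receive one of the two treatment sequences", using "permutated balanced blocks with random block length", stratified by site and by genetic versus sporadic ataxia.

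The section on analyses for primary and secondary endpoints gives the primary mixed model for the change in SARA total score. Its terms are "fixed effects: factor for treatment, visit, treatment-by-visit interaction, and mean of both period-level baseline SARA total scores as covariate", plus patient-level random intercepts and slopes. Neither period nor sequence appears. The same section computes the change at the two-week and six-week visits of each treatment period, and that fixes the natural meaning of visit. The model is a default that the statistical analysis plan may revise.

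The further adjusted analyses cover type of ataxia, gender, age, site and physiotherapy, but not period. The descriptive end-of-period comparisons "will be performed using a two-sided Wilcoxon signed rank test", again without regard to period.

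**The concern.** In a two-period crossover, each patient's active-minus-placebo difference contains the treatment effect plus or minus any difference between the periods, with the sign set by the sequence. A period term removes that component. Nothing in the listed model does so:

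- Visit, read as week 2 or week 6, takes the same values in both periods.
- The baseline covariate is one mean per patient, so it cannot distinguish the periods.
- The wash-out argument under trial procedures concerns carry-over, which is a different matter.

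A difference in mean change between periods is plausible. Raters and patients repeat the same tests over many visits, and expectation may be strongest in the first period. The footnotes to the schedule also let the eligibility SARA serve as the period-1 baseline, which invites regression to the mean in period 1 only. At stake are the calibration of the confirmatory test and, if the sequences end up unequal, the treatment estimate itself.

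**Working it through.** **The plan's own figure.** The inputs come from the sample-size section: difference 1.5, SD 4.2 used as the SD of the paired difference, a paired t-test "with a 0.05 two-sided significance level", and a design that "will have 90% power to detect a difference in means of 1.5". The noncentral t gives n = 85 (power 90.2%). Rounded up to 86 for two sequences, power is 90.6%. With 20% dropout, 86/0.80 = 107.5, so 108. The stated 86 and 108 reproduce.

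**Set-up.** Score improvement as positive. Let τ be the treatment effect and π the period-2-minus-period-1 shift in mean six-week change. The active-minus-placebo difference has mean τ − π in the active-first sequence (AP) and τ + π in the placebo-first sequence (PA). Averaged over all completers without a period term:

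- expected estimate = τ + π × (n_PA − n_AP)/N
- SD of the pooled differences when balanced ≈ √(4.2² + π²)

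With a period term, the estimate is the mean of the two sequence means. It is unbiased for any π, and the SD stays at 4.2.

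**Balanced sequences (43/43), n = 86, τ = 1.5.** The shifts are assumptions.

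| Assumed shift π | SD without period term | Formula power |
|---|---|---|
| 0 | 4.20 | 90.6% |
| 0.5 | 4.23 | 90.2% |
| 1 | 4.32 | 89.0% |
| 2 | 4.65 | 84.0% |

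The formula is somewhat pessimistic. The shift inflates the estimated standard error, but the true sampling SD of the mean is still 4.2/√86. At π = 2, a direct approximation is Φ(1.5 × √86/4.2 − 1.988 × 4.65/4.2) = Φ(3.31 − 2.20) ≈ 87%, and simulation also gives about 87%. Under the null, the same reasoning gives a size of 2 × Φ(−2.20) ≈ 3% instead of 5%, so the test is conservative.

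**Unequal completers.** Bias per 1-point shift:

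- 40/46: 6/86 = 0.07 points
- 36/50: 14/86 = 0.16 points

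The sign depends on which sequence loses more patients, so the error can favour either arm. At 36/50 with π = 2, the bias is 0.33 points and the simulated size is about 7%. The period-adjusted analysis stays at about 5%.

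**How likely are such splits?** Start from 54/54 and drop 108 − 86 = 22 patients at random with respect to sequence. A gap of at least 6 in either direction (40/46 or worse) has hypergeometric probability of about 23%. A gap of at least 14 (36/50 or worse) has about 0.15%.

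**The case against.** The model is explicitly provisional, and the analysis plan, which is not shown, may already include period. That is fair, but the article publishes a complete list of fixed effects as the default. The omission is therefore a stated choice and not a detail left for later.

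Several stronger readings are tempting and do not hold:

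- **That progression makes a period effect likely.** The background says "most types of CA are progressive and therefore become more disabling in the course of the disease". The endpoint, however, is change from each period's own baseline. Steady progression adds equally to both six-week changes and cancels; only a different rate of change in period 2 would produce a shift.
- **That the term list fails however visit is coded.** If visit meant the four study visits (3, 4, 6 and 7), period would be absorbed. Each single-visit contrast would then compare sequences between patients, but the average of the visit 4 and visit 7 contrasts recovers the period-adjusted crossover estimate. The wording favours week 2 and week 6 in any case.
- **That substantial bias is to be expected.** Blocked 1:1 allocation keeps entry numbers close to balance, and patients who stop medication are asked to keep attending. A 36/50 split would in practice need dropout related to sequence, for which the article gives no evidence. Shifts of 1 to 2 points are large against a target effect of 1.5.
- **That the signed-rank tests carry the same weight.** They are labelled descriptive, and their use is conditional on the blinded data review.

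What stands is that a period shift, if present, is not removed by anything in the stated model.

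**Conclusion.** The point holds as a correctable weakness in the default primary model. It should be fixed, but it does not threaten the trial's validity. With balanced sequences the estimate is unbiased, and the cost is a wider interval and a conservative test: under half a percentage point of power at a 0.5-point shift, 1.6 points at 1, and about 4 (simulated) to 7 (formula) at 2. Bias requires both a period shift and unequal completers; at 40/46 it is 0.07 points per point of shift.

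The shifts and splits are assumptions, since the article gives neither. The figures come from the paired-difference analysis that underlies the sample size. The effect in the planned mixed model, with its random intercepts and slopes, has not been quantified.

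**What to change.** Before unblinding, make these changes in the statistical analysis plan:

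1. Add period as a fixed effect in the primary mixed model, and sequence if wanted.
2. State that visit means week 2 or week 6 within a period.
3. As a minor matter, for the descriptive end-of-period comparisons, replace the signed-rank test by a Wilcoxon rank-sum test between the two sequences on the within-patient period-1-minus-period-2 differences. These centre on τ − π and −τ − π, so half the two-sample Hodges-Lehmann shift estimates τ.

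The cost is wording and, for the period term, one degree of freedom. In the paired-difference analysis, power with the period term and 43/43 completers stays at 90.6% whatever the shift. Adding the term after unblinding would be a post hoc change to a confirmatory model, so the timing matters more than the effort.

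### The primary model's covariate needs a visit 5 SARA score, so patients with period-1 data but no visit 5 fall out of an analysis meant to include everyone randomised

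*Protocol article*

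**What the plan says.** The Protocol article, under Statistical analyses for primary and secondary endpoints, sets out a linear mixed model for the change in SARA total score, subject to revision in the SAP. Its patient-level covariate is the "mean of both period-level baseline SARA total scores as covariate". Table 2 and the section on Investigative drug and placebo place the two period starts at visit 2 (day 0) and visit 5 (day 70).

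The same section commits to an intention-to-treat analysis in which "all participants randomized will be analyzed according to the treatment sequences to which they were allocated and irrespective of the extent of intervention received". It then defines a full analysis set that should come as near to this as it can. It justifies the mixed model partly by the need to handle visits that are missed or off schedule.

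Under Power considerations and sample size calculation, the authors write "we expect a dropout rate of about 20" per cent, without saying when in the trial those patients are expected to leave. The section on participants who go off protocol asks patients who stop medication to keep attending the scheduled visits, and offers phone or mail contact to those who will not or cannot.

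**The concern.** A mixed model copes with missing outcomes. It does not cope with a missing covariate: a row without a covariate value contributes nothing. A mean of two baselines is undefined when one was never measured. So a patient who attended visit 3 or visit 4 but not visit 5 would lose SARA changes that were actually observed in period 1.

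Entry to the primary analysis would then depend on reaching visit 5, an event that follows randomisation and the first treatment. The observed period-1 changes are what allow a likelihood-based model to correct for dropout related to earlier response. Discarding them removes that protection for the very patients who need it.

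**Working it through.** **Step 1. The plan's own figures.** Inputs: "90% power to detect a difference in means of 1.5"; "a standard deviation of the individual SARA change of 4.2"; two-sided alpha of 0.05; paired t-test. With the noncentral t distribution, the smallest n with at least 90% power is 85 (power 0.902), and 86 gives 0.906. This matches "a sample size of 86 (85 is calculated but 2 sequences are needed) in total". Enrolment: 86 / 0.80 = 107.5, rounded up to 108, which matches "a total of 108 patients have to be enrolled". The figures reproduce, and they already presuppose 86 complete pairs.

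**Step 2. Who is affected.**
- No SARA after visit 2: no change score exists, so the patient is lost under any covariate.
- SARA at visit 3 or 4 but not at visit 5: a period-1 change exists but the mean of both baselines does not. The data are lost as the model is written, and this loss is avoidable.
- SARA at visit 5, with later visits missing: the covariate exists and the patient stays in.

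Only the middle group matters here. Period-2 changes are undefined for that group in any case, because they need the visit 5 baseline. What is at stake is period-1 data.

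**Step 3. How many.** Expected dropouts: 108 × 0.20 = 21.6. The share falling in the middle group is not stated. For assumed shares of 25%, 50% and 100%, the counts are 21.6 × 0.25 = 5.4, 21.6 × 0.50 = 10.8 and 21.6 × 1.00 = 21.6. So 22 is a ceiling.

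**Step 4. Precision.** Let ρ be the correlation between a patient's two period changes (assumed). The variance of one period's change is s² = 4.2² / [2(1 − ρ)].
- As written, with 86 pairs: information 86 / 17.64 = 4.875, SE = 1/√4.875 = 0.453. Power is Φ(1.5/0.453 − 1.96) = 0.912 (normal approximation; the exact t value is 0.906).
- With 22 period-1-only patients kept, 11 per sequence, ρ = 0.2: s² = 17.64/1.6 = 11.025. Added information is 22/(4 × 11.025) = 0.499, total 5.374, SE 0.431, power 0.935.
- The same at ρ = 0.5: s² = 17.64, added information 22/(4 × 17.64) = 0.312, total 5.187, SE 0.439, power 0.927.

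Keeping these patients gains a little precision. Losing them does not bring the trial below its 90% target.

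**Step 5. Bias.** Simulation with true effect −1.5, 108 patients (54 per sequence), 4,000 runs per scenario, one end-of-period change per period, a random patient intercept and known variances. No baseline covariate was fitted; the as-written analysis simply keeps only patients with both baselines. All dropouts leave after period 1 is observed and before visit 5. Where dropout is not random, it depends on the observed period-1 change. Each cell shows ρ = 0.2, then ρ = 0.5.

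| Dropout mechanism | Mean number lost | As written | Period-1 data kept |
|---|---|---|---|
| Completely random | 21.5; 21.7 | −1.51; −1.49 | −1.50; −1.50 |
| Non-improvers leave, either treatment | 22.2; 24.6 | −1.44; −1.45 | −1.51; −1.50 |
| Response-related, mainly active-first | 21.0; 21.8 | −1.87; −1.83 | −1.50; −1.49 |
| Response-related, mainly placebo-first | 20.9; 21.8 | −1.13; −1.17 | −1.50; −1.51 |

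The as-written estimates have a standard deviation of 0.44 to 0.46 across runs. The last two rows show shifts of 0.33 to 0.37 points, in opposite directions.

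**The case against.** The best defence is that nothing in the article says these patients will be excluded. The model is expressly provisional, further detail is promised in the SAP, and how to compute a covariate with a missing component is an ordinary SAP matter. The full analysis set wording also admits some shortfall from all randomised patients. This stands in part: the SAP may already have settled the point, and the exclusion follows from the stated covariate rather than from an explicit rule. But the article does name a covariate, that covariate cannot be computed for these patients, and the default applies unless it is changed. A set meant to be as full as it can be should not lose observed outcomes through a choice of covariate.

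The defence is also right that the bias needs particular conditions. With an equal response-related loss of 11 patients per sequence, the estimate stays at about −1.50. With a moderate response-related loss of 14 against 8, it moves only to −1.57 to −1.61, against an SE of about 0.45.

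A reader might infer that patients who stop treatment for intolerance or lack of benefit are removed as such. The article does not support that: it asks them to attend every scheduled visit, and only a missing visit 5 SARA removes them. Nor does that request close the gap, because SARA is rated by an examiner and phone or mail contact is unlikely to supply it.

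A reader might also infer that residual drug effect at visit 5 contaminates the covariate and biases the result. The covariate is one value per patient and largely cancels from the within-patient contrast. The article also states its assumption that the wash-out is long enough to prevent carry-over. That reading is not supported.

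**Conclusion.** The point holds, as something that should be fixed rather than something that must be. Followed literally, the default primary model drops observed period-1 changes for patients with a visit 3 or visit 4 SARA and no visit 5 SARA. This is at odds with two statements in the same section.

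The number affected lies between none and about 22 of 108. It is probably well below the ceiling: some dropouts will leave before visit 3, some after visit 5, and some who stop medication will still attend. It would be wrong to read 22 as a forecast, or to conclude that the trial is underpowered.

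The harm is possible bias, and it requires dropout that is related to response and differs between sequences. The simulated shifts of 0.33 to 0.37 points rest on strong assumptions about mechanism and timing and on assumed correlations of 0.2 and 0.5; they illustrate the mechanism and do not predict the result. Keeping period-1 data removed the bias because dropout in those scenarios depended only on observed period-1 changes. If it depended on unobserved values, no choice of covariate would guarantee protection.

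**What to change.** State in the SAP, before unblinding, that the covariate is the mean of the available period-level baseline SARA scores, and that patients with period-1 data only stay in the primary model. For those patients the covariate is then the visit 2 score. For complete pairs the model is unchanged, and both periods are still treated alike.

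Using the visit 2 score for everyone is an acceptable alternative. It is measured by the time of randomisation, but it is a component of the period-1 change and not of the period-2 change.

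Either option costs a sentence or two and no new data. Because the covariate is constant within a patient, the effect on the within-patient contrast for complete pairs is negligible. If the SAP already contains such a rule, it is enough to confirm it.
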